5. ECOG-PS
6. American Society of Anesthesiologists (ASA) Physical Status Classification
7. Sleep apnea-related items (STOP-Bang questionnaire, Mallampati score, and submental soft-tissue excess)
8. 12-lead ECG
9. Chest X-ray
   - 1. **Examination, Testing and Evaluation**
        1. **During Treatment**
10. Sedation start/stop times
11. Subjective and objective findings
12. Vital signs: blood pressure, mean blood pressure and heart rate.

Blood pressure will be taken at 5-minute intervals, other items will be taken at 2.5-minute intervals for 15 minutes after the start of sedation, and at 5-minute intervals thereafter. Measurements will also be taken as required at the discretion of the doctor in charge of sedation. Collect the data for the worst levels (highest or lowest).

1. Monitor (CSM-1901) data
2. Record any ECG monitor abnormalities.
3. SpO_2_: <90% (frequency and duration), <95% (frequency)
4. Apnea (≥20 sec) frequency
5. Respiratory status under SpO_2_ of <90% and <95%
6. False alarm frequency
7. Technical trouble and bodily movement frequency
8. Response to respiratory abnormality
9. BIS
10. Ramsay sedation scale

To be carried out after the commencement of sedation when the condition is stable, and to be reconsidered as required whenever the depth of sedation changes.

1. Support therapy
2. Observation of adverse events
   - - 1. **At the End of Treatment**
3. Subjective and objective findings
4. Vital signs: heart rate, blood pressure, temperature, SpO_2_ and respiration rate
5. Ramsay sedation scale
6. Sedative dose
7. Coordination during procedure (VAS)
8. Observation of adverse events
   - - 1. **After Procedure (30 min, 1 hr, 2 hrs and 3 hrs)**
9. Subjective and objective findings
10. Vital signs: heart rate, blood pressure, temperature, SpO_2_ and respiration rate
11. Monitor (CSM-1901) data
12. SpO_2_: <90% (frequency and duration), <95% (frequency)
13. Apnea (≥20 sec) frequency
14. Respiratory status under SpO_2_ of <90% and <95%
15. Ramsay sedation scale
16. Support therapy
17. Observation of adverse events
    - - 1. **Following Day**
18. Subjective and objective findings
19. Vital signs: heart rate, blood pressure, temperature and SpO_2_
20. Degree of satisfaction with treatment (VAS)
21. Support therapy
22. Observation of adverse events
23. **Handling Adverse Events**
    1. **Definition of Adverse Event**

An adverse event refers to an
undesired or unintentional sign (including abnormal fluctuations in clinical data), symptom or disease that appears after the commencement of the study, regardless of the causal relationship with the testing equipment.

- 1. **Definition of Disease, etc.**

Disease, etc., refers to an illness, disorder, death or infectious disease that is suspected to have occurred due to the carrying out of a particular clinical study, including abnormal clinical test data and other symptoms (referred to as adverse events that have an undeniable causal relationship with the particular clinical study). Moreover, if a defect is detected in a medical device used in the study and it is suspected that it may cause disease, etc., this will also be reported.

Matters regarding diseases, etc., that must be reported to the Authorized Clinical Study Review Board/Minister of Health, Labour and Welfare are determined in “9.3. Reporting Diseases, etc., and Defects.”

- 1. **Dealing with Participants when Adverse Events Occur**

When an adverse event is observed, the principal investigator or assistant investigators will immediately take appropriate measures, and if treatment is required they will inform the participant.

- 1. **Obtaining Information regarding Adverse Events**

With regard to all adverse events that occurred during the reporting period shown below, the principal investigator or assistant investigators will enter them in medical records and case report forms truthfully.

- 1. **Adverse Event Reporting Period**

All adverse events that occur between the first date on which the testing equipment is used and the day following the last day on which the testing equipment is used will be collected regardless of the causal relationship. Adverse events that are deemed to have a causal relationship with the testing equipment will be observed until such adverse events disappear or the symptoms stabilize.

All serious adverse events that occur before seven days after the last day on which the testing equipment is used will be reported, and such adverse events will be observed until they disappear or the symptoms stabilize. Adverse events that are deemed not to have any relationship with the testing equipment will be observed until they disappear or for 28 days after the completion (discontinuation) of the study.

The principal investigator or assistant investigators will enter all of the adverse events that occurred during the reporting period shown above in medical records and case report forms truthfully.

- 1. **Reporting Details Required for Evaluating Adverse Events**

1. Name of the adverse event.
2. Date on which the event occurred.
3. Date on which the outcome was decided.
4. Outcome: recovered (or disappeared), alleviated, recovered or disappeared with aftereffects, yet to recover, deceased, or unknown.
5. Procedure (use of testing equipment): as scheduled, discontinued, or not-applicable.
6. Other procedures: none, drug therapy, or other.
7. Severity: Not severe or severe.
8. Symptom evaluation: CTCAE (Ver. 4.0) Grade 1, 2, 3, 4 or 5.
9. Causal relationship with testing equipment: Yes, no.
10. Predictability: Known or unknown
    - 1. **Adverse Event Recoverability and Causal Relationship with Testing Equipment**

The disappearance of an adverse event refers to the state of the patient without the adverse event in question or the recovery of a patient to the state prior to the use of the equipment. The causal relationship between an adverse event and the testing equipment will be determined in light of the general condition of the patient, complications, concomitant drugs/therapies, and time factors. When it is unknown whether there is causal relationship between an adverse event and the testing equipment, such cases will be entered as “Yes” under Causal Relationship.

- - 1. **Adverse Event Predictability Evaluation**

The principal investigator will refer to the document that shows the latest overview of the testing equipment (package insert/operation manual, etc.) and determine the predictability of adverse events. Adverse events for which it is impossible to predict occurrence tendencies from the summary documents for such equipment, such as the number of instances of the adverse event occurring, or the frequency of occurrence or prerequisites for the appearance of a particular adverse event, shall be entered as “unknown” and where they can be predicted they shall be entered as “known.” As there is no existing summary document for the nasal pressure monitor, the package insert for a portable sleep apnea tester will be used for reference.

- 1. **Expected Adverse Events**
     1. **Expected Adverse Events Associated with ERCP, EUSFNA, ESD and DBE**

Expected adverse events associated with ERCP, EUSFNA, ESD and DBE include acute pancreatitis, acute cholangitis, bleeding, infection, gastrointestinal perforation, peritonitis and aspiration pneumonia.

- - 1. **Adverse Events due to Propofol**

Potential adverse events caused by propofol include hypotension, anaphylactoid symptoms, bronchospasm, pharyngeal obstruction, transient apnea, epileptic-like movements, bradycardia, ventricular extrasystole, left bundle branch block, pulmonary edema, delayed emergence, and rhabdomyolysis.

- - 1. **Adverse Events due to Fentanyl**

Potential adverse events caused by fentanyl include drug dependence, respiratory depression, respiratory distress, blood pressure reduction, shock, arrhythmia, agitation, and cyanosis.

1. **Handling Serious Adverse Events**
   1. **Definition of Serious Adverse Event**

A serious adverse event is defined as one that corresponds to any of the following.

(1) Death

(2) An event that may lead to death.

(3) Impairment (the appearance of functional failure of such a degree that it hinders daily life).

(4) An event that may lead to impairment.

(5) An event that requires hospitalization or an extension of hospitalization in a hospital or clinic for treatment.

(6) A serious event similar to the cases described in (1) to (5).

(7) A congenital disease or abnormality.

Note: The “hospitalization’ mentioned in (5) does not include hospitalization or extension of hospitalization for retesting, follow-up testing or treatment, or hospitalization for the purpose of treatment or testing that was already scheduled to be performed during the timeframe of the study (scheduled surgery and testing). (However, events that newly occur during such hospitalization will be handled as an adverse event.)

- 1. **Serious Adverse Events Subject to Reporting**

All serious adverse events that occur during the study, and other serious adverse events that are suspected to have occurred due to testing equipment after the completion (discontinuation) of the study, will be reported.

Acute cardiorespiratory failure that occurs during the period in which adverse events are observed within the study period (from the commencement of sedation to the following day) will be defined as follows in accordance with CTCAE. Adverse events classed as Grade 3 or above will be reported as serious adverse events regardless of the causal relationship with the testing equipment.

| Grade 3 | Events that are not life-threatening, but which require general management using tracheal intubation or general anesthesia even after the measures described in “5.7. Response to Respiratory Abnormalities” as defined in the Protocol have been taken. |
| --- | --- |
| Grade 4 | Events that require resuscitation using cardiac massage and tracheal intubation due to deterioration in cardiovascular dynamics. |
| Grade 5 | Death. |

- 1. **Reporting Disease, etc., and Defects**

When the principal investigator comes to the knowledge regarding the disease/condition that are listed in the table below during the execution of the specific clinical study, they will report within the specified period.

**Table: Reporting Diseases, etc. (For Specific Clinical Study involving Medical Devices that are Unapproved or Not Listed for Use under National Health Insurance)**

|  |  |  | Report to the Pharmaceuticals and Medical Devices Agency (PMDA) | Report to Clinical Study Review Board |
| --- | --- | --- | --- | --- |
| Disease, etc. | Unknown | Death | 7 days | 7 days |
|  |  | Serious | 15 days | 15 days |
|  |  | Non-serious |  | Regularly |
|  | Known | Death |  | 15 days |
|  |  | Serious |  | Regularly |
|  |  | Non-serious |  | Regularly |

If a defect is found in the testing equipment used in the study that may cause a serious disease, etc., after reporting the matter to the participating institution within 30 days of coming to know about it, the principal investigator will report it to the Approved Clinical Study Review Board. Reporting procedures shall be in accordance with “9.4. Serious Adverse Event (disease, etc.,/defect) Reporting Procedure.”

**Table: Reporting Defects in Specific Clinical Studies involving Medical Devices that are Unapproved or Not Listed for Use under National Health Insurance**

|  |  |  | Report to the Pharmaceuticals and Medical Devices Agency (PMDA) | Report to Clinical Study Review Board |
| --- | --- | --- | --- | --- |
| Defect  (medical device) | Unknown | Risk of death |  | 30 days |
|  |  | Risk of serious adverse event |  | 30 days |
|  |  | Risk of non-serious event |  |  |
|  | Known | Risk of death |  | 30 days |
|  |  | Risk of serious adverse event |  | 30 days |
|  |  | Risk of non-serious adverse event |  |  |

- 1. **Serious Adverse Event (Disease, etc./Defect) Reporting Procedure**

In cases where an adverse event occurs and the principal investigator determines that it is serious, information regarding the adverse events will be handled in accordance with the following procedure.

1. Report from the principal investigator to the head of the participating institution

The principal investigator reports to the head of the participating institution regarding information concerning the adverse event regardless of the causal relationship as promptly as possible. First an Emergency Report (Report 1) is sent, and then a Detailed Report (Report 2) will follow.

1. Report to the Approved Clinical Study Review Board/Minister of Health, Labour and Welfare

In accordance with the Clinical Trials Act, in cases where the principal investigator determines that reporting to the Approved Clinical Study Review Board/Minister of Health, Labour and Welfare is required as described in “9.3. Reporting Diseases, etc. and Defects,” the principal investigator will prepare a Medical Device Diseases, etc., and Defect Report (Standard Form 9) and a Diseases, etc., Report (Medical Device) (Annex Form 2-2), and submit them to the Approved Clinical Study Review Board/Minister of Health, Labour and Welfare. Regular reports regarding diseases, etc., will be made to the Approved Clinical Study Review Board using the Regular Report Form (Standard Form 5).

1. Information Shared with Manufacturers/Retailers of Testing Equipment

When making 7-day or 15-day reports regard diseases, etc., such information will also be shared with manufacturers/retailers of testing equipment at the same time.

1. Handling Additional Information

When the principal investigator of the participating institution where the adverse event in question occurred acquires additional information regarding the adverse event, an additional report will be made to the head of the participating institution as promptly as possible. Procedures for handling additional information will be in accordance with 2) to 4) of this section.

1. Response based on the Pharmaceutical and Medical Device Safety Information Reporting System.

Post-marketing drugs will be handled based on the Pharmaceutical and Medical Device Safety Information Reporting System, and reports will be submitted to the Ministry of Health, Labour and Welfare as required.

- 1. **Regular Reports**

Regular reports will be submitted to the Approved Clinical Study Review Board and the Minister of Health, Labour and Welfare regarding diseases, etc., in accordance with the Clinical Trials Act. Regular reports will be submitted to the Approved Clinical Study Review Board as a rule each year after one year from the day on which the study plan was submitted to the Minister of Health, Labour and Welfare, within two months of the completion of such period. Reports to the Minister of Health, Labour and Welfare will be made within one month of the day on which the Approved Clinical Study Review Board expressed their opinion.

1. **Evaluation Items**
   1. **Primary Endpoint**

- Hypoxemia occurrence rate (SpO_2_ <90%): number of cases / total number of eligible participants

Basis for Primary Endpoint Selection

This particular clinical study will be conducted to verify that there is no difference in the frequency of hypoxemia between the nasal pressure monitor group and the capnography group. SpO_2_<90% will be used as the general index for hypoxemia.

- 1. **Secondary Endpoints**

**Secondary Endpoints for Usefulness**

- Frequency of apnea (≥20 seconds)
- Degree of participant satisfaction (VAS)
- Coordination during procedure (VAS)

**Secondary Endpoints for Safety**

Adverse Event Occurrence Rate

NCI-Common Terminology Criteria for Adverse Events v4.0 (CTCAE Ver. 4.0) JCOG version will be used to evaluate adverse events.

Basis for Secondary Endpoint Selection for Usefulness

Items where a difference in occurrence frequency between the capnography group and the nasal pressure monitor group is considered to be important will be evaluated as secondary endpoints.

Basis for Secondary Endpoint Selection for Safety

General evaluation standards will be used.

- 1. **Exploratory Endpoints**
- Comparison with capnography waveforms.
- Waveform analysis at the time of respiratory abnormality.
- Consideration of respiratory abnormality-related risk factors (including obesity, age, history of smoking, drug administration dose, treatment duration, and SAS).

Basis for Exploratory Endpoint Selection

There is a possibility that nasal pressure monitoring can detect the minute changes in waveforms that appear prior to the appearance of a respiratory abnormality. We will compare the changes in the waveforms prior to any drop in SpO_2_ between the capnography group and the nasal pressure monitor group, and analyze to what degree the monitor observer is able to detect changes in waveforms. As there is also a possibility that nasal pressure monitoring can accurately detect the patterns for respiratory depression and obstructive ventilatory impairment, we will analyze the frequency of those events in both groups. We will also consider the relationship between respiratory abnormalities (hypoxemia, apnea and obstructive ventilatory impairment) and obesity, age, drug dose, procedure duration and SAS in order to identify factors relating to respiratory abnormalities.

1. **Statistical Considerations**

The statistical analysis plan overview for the clinical study is shown below. Statistical analysis plan details are contained in the Statistical Analysis Plan. Although the overview of the Study Protocol for the clinical study may be revised in the Statistical Analysis Plan, in cases where the primary endpoint definition or analysis method is to be changed, the Study Protocol will be revised.

- 1. **Analysis Population**
     1. **Full Analysis Set (FAS)**

The FAS will be all registered participants whose usefulness data is entered after randomization. However, those of them whose baseline data was not available and those who are seriously in bleach of the Study Protocol (no consent, registered outside the agreed period) will be excluded.

- - 1. **Per protocol set (PPS)**

PPS will be the population of FAS minus those cases that are seriously in bleach of the Study Protocol, in terms of research method or concurrent therapy.

1. Selection criteria violation
2. Exclusion criteria violation
3. Contraindicated drug violation
4. Contraindicated therapy violation
   - 1. **Safety analysis set (SAS)**

SAS will the registered patients who were fitted with the testing equipment (the monitor) at least once and underwent endoscopy under sedation.

- 1. **Target Number of Cases and Basis for Selection**

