| **Study Method** | A single-arm study to evaluate the safety of the nasal pressure monitor will be carried out with patients who undergo invasive endoscopy, followed by a randomized comparative study to validate its usefulness. In the randomized comparative study, patients will be single-blinded and divided into two groups: a nasal pressure monitor group and a capnography group. Sedatives will be administered to each group based exclusively on data from their respective monitors.  Sedation of both groups will be carried out using propofol and fentanyl. The sedation depth in each group will be kept between 60 and 80 on the bispectral index (BIS) using the respective monitor. Monitoring will continue until three hours after the completion of the endoscopic procedure. |
| **Target No. of Patients** | Safety Evaluation (Phase II): 45  Usefulness Evaluation (Phase III): 224 (112 in each group) |
| **Study Period** | ● Overall duration: 24 months (from the initial announcement on the Japan Registry for Clinical Trials (jRCT) until August 31, 2021)  * Detailed Schedule  Safety Evaluation (Phase II): 10 months (from the initial announcement on the jRCT until June 30, 2020)  Usefulness Evaluation (Phase III): 20 months (from January 1, 2020 until August 31, 2021)  ● Registration period: 18 months (from the initial announcement on the jRCT until February 28, 2021)  * Registration Details  Registration for Safety Evaluation (Phase II): 4 months (from the initial announcement on the jRCT until December 31, 2019)  Registration for Usefulness Evaluation (Phase III): 14 months (from January 1, 2020 until February 28, 2021) |
| **Number of Participating Institutions** | One |
| **Ethics Policy** | This clinical study will be carried out in compliance with ethical principles and clinical study methods based on the Declaration of Helsinki and other related regulatory requirements. |
| **Authorized Clinical Study**  **Review Board** | Prior to the commencement of this clinical study, the Authorized Clinical Study Review Board of the participating institution will examine the ethical, scientific and medical appropriateness of of the study. The study will commence after approval has been received from the Authorized Clinical Study Review Board. The Authorized Clinical Study Review Board will continue to review the performance of the study at least once a year. |

1. **Introduction**

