Nasal pressure monitoring has the following merits over capnography: 1) It is not affected by carbon dioxide supply, 2) it reflects the semiquantitative change in single ventilation volume, and 3) changes in waveforms help differentiate obstructive and central respiratory abnormalities. The ability to distinguish between central respiratory abnormalities due to excessive drug administration and pharyngeal airway obstruction that requires airway management on the basis of waveform patterns makes it possible to take appropriate measures earlier and prevent the development of severe hypoxemia.

1. **The Objectives and Necessity of Research**

The objectives of this study are to confirm the safety of patient respiration status monitoring using a nasal pressure monitor that is an unapproved medical device still currently under development for use with patients undergoing invasive endoscopy (ERCP, ESD, EUS-FNA and DBE), and to evaluate its usefulness by comparing with capnography. As mentioned above, although capnography is currently a popular option for use in clinical practice, a number of problems have been pointed out. If we can therefore show the usefulness of the new respiration monitor, which is expected to be able to detect respiratory abnormalities and their cause prior to the development of hypoxemia, this will have a significant impact on clinical practice.

1. **Eligible Participants**
   1. **Selection Criteria**

Patients who undergo invasive endoscopic treatment (ERCP, ESD, EUS-FNA or DBE) under sedation at the Endoscopy Center of Chiba University Hospital and who meet the following criteria, but not the exclusion criteria.

1. Aged 20 years or older (regardless of sex)
2. Patients who receive a thorough explanation regarding participating in the study prior to the commencement of the study, and who provide their written consent.
3. Patients with SpO2 of ≥95% (room air).
4. Patients with systolic pressure of ≥90 mmHg.
   1. **Exclusion Criteria**
5. Patients who regularly take an oral opioid formulation or oral benzodiazepine (with the exception of cases where it is taken internally as a sleep inducer before going to bed).
6. Patients who register with another clinical study within four weeks of registering for this study.
7. Patients with a drug abuse problem or whose physical, psychological or social circumstances may hinder their participation in the study or interfere with the evaluation of the results of the study.

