| After entering the treatment room for invasive endoscopy | For the Safety Evaluation (Phase II), patients will be fitted with both a capnography monitor and a nasal pressure monitor. After the nasal pressure monitor is fitted, do not turn on the capnography monitor, only check the display of the nasal pressure monitor, and administer sedatives. The capnography waveforms will be recorded and used later for waveform analysis along with those from the nasal pressure monitor.  Propofol and fentanyl will be used as sedatives, and will be administered by an endoscopist who has been fully trained in sedation by an anesthesiologist. The strength of the sedatives during the procedure will be controlled between BIS 60 and 80 as shown on the monitor in both groups. Prior to the administration of sedatives, oxygen will be administered through a transnasal catheter at a rate of 2 l/min. Local pharyngeal anesthesia (8% lidocaine spray) will be sufficiently administered until the vomiting reflex disappears. Propofol and fentanyl will be administered in accordance with a predetermined protocol (see below), while monitoring the patient’s sedation depth and suitably adjusting the dose of each drug. Administration will be stopped when the procedure has been completed, and if respiration rate drops to ≤8 bpm, naloxone will be administered. Patient response will be verified by calling out to the patient, and after checking that there are no cardiorespiratory dynamic problems, the patient will be allowed to leave the treatment room.  In cases where SpO_2_ is observed to have declined (<90), apnea lasts for ≥20 seconds, or a respiratory abnormality (≤8 bpm or abnormal waveform) accompanied by a decline in SpO_2_ (<95%) is observed during sedation, the doctor in change of sedation will report the respiratory abnormality to the endoscopy team, and measures will be taken to improve respiration (see 5.7). When such measures have been taken, details regarding the respiratory abnormality that caused them are recorded in the check sheet.  Monitoring data will be analyzed for up to three hours after the treatment in the Safety Evaluation (Phase II). Later, assistant investigators will analyze the monitor waveforms. |

● Usefulness Evaluation (Phase III)

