If SpO_2_ is 90–94%, first increase the oxygen supply (maximum of 6 l). If SpO_2_ does not improve, if the cause can be assumed from the monitor waveforms, deal with the cause. That is to say, in cases of apnea, infrequent respiration or low respiration, stimulate the patient, reduce and/or stop propofol and fentanyl, and in cases of obstructive ventilatory impairment, maintain airway patency. In cases where apnea that lasts for ≥20 seconds is observed without a decline in SpO_2_, the doctor in charge of sedation will consider response measures, including observation.

- 1. **Standards for Discontinuation in Individual Cases**

In cases where the following criteria are met, the principal investigator or assistant investigators will discontinue the study. However, testing and evaluation will be continued according to the schedule.

1. When adverse events occur that make the continuation of the study difficult, and the principal investigator or assistant investigators decide it is necessary to discontinue the study.
2. When eligible participants request it to be discontinued.
3. In other cases where the principal investigator or assistant investigators decide that it is impossible for eligible participants to continue with the study.
4. When the Research Administrator decides to discontinue the study.

In cases that correspond to items other than 1) above, the date on which the study is discontinued shall not be the date on which the event occurred that caused such discontinuation, but the date on which the principal investigator or assistant investigator decides to discontinue the study.

- 1. **After the Completion of the Study**

Even after the completion of the study we will endeavor to make the best prevention, diagnosis and treatment methods obtained from the results of the study available to eligible participants of the study.

1. **Testing Equipment**
   1. **Testing Equipment Overview**

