| Oxygen desaturation (<90%)  oxygen desaturation (<90%) |  | ●b |  | ●b | | | |  |
| Oxygen desaturation (<95%)  oxygen desaturation (<95%) |  | ●b |  | ●b | | | |  |
| False alarm frequency |  | ●c |  | ●c | | | |  |
| Response to respiratory abnormality |  | ● |  |  |  |  |  |  |
| Technical trouble frequency |  | ●d |  |  |  |  |  |  |
| Position change frequency |  | ●d |  |  |  |  |  |  |
| BIS |  | ● |  |  |  |  |  |  |
| Sedative dose |  |  | ● |  |  |  |  |  |
| Coordination during treatment |  |  | ●e |  |  |  |  |  |
| Satisfaction with drug therapy |  |  |  |  |  |  |  | ●e |
| Support therapy |  | ● |  | ● | ● | ● | ● | ● |
| Observation of adverse events |  | ●f | ●f | ●f | ●f | ●f | ●f | ●f |

In some cases, data acquired prior to obtaining consent may be included in the study data. X-ray images and ECG data shall be acquired no more than 60 days prior to obtaining the consent of patients, and when no apparent heart disease or lung disease is observed, the use of such data is permitted and requires no retesting.

a: During treatment in the Safety Evaluation (Phase II), blood pressure, heart rate, SpO2, BIS and capnography/nasal pressure waveforms will be continuously recorded, while the doctor in charge of sedation monitors all items other than capnography waveforms. During the procedure that undergoes Usefulness Evaluation (Phase III), only one of capnography or nasal pressure will be recorded and displayed. After returning to the ward, SpO2 and capnography/nasal pressure waveforms (the same as those recorded during treatment) will be continuously recorded for a further three hours (one hour in the case of the usefulness evaluation).

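### Section 10.3 compares waveform detection between the randomised arms only ahead of an SpO2 drop, an outcome the assigned monitor can change, and reads no drop-free windows for contrast

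*Protocol*

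**What the plan says.** The basis for the exploratory endpoints in section 10.3 of the Protocol states: "We will compare the changes in the waveforms prior to any drop in SpO_2_ between the capnography group" and the nasal pressure group. The same sentence adds that the investigators will "analyze to what degree the monitor observer is able to detect changes in waveforms". So the contrast is between arms, the measure is detection, and the material is the waveform ahead of a fall in SpO2. Section 10.3 gives no SpO2 threshold for that fall.

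Other parts of the Protocol bear on this:

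- **Care follows the monitor.** The Study Outline says of Phase III: "Sedatives will be administered to each group based exclusively on data from their respective monitors".
- **The monitor is meant to prevent the drop.** Section 1 argues that telling the causes of abnormal breathing apart "makes it possible to take appropriate measures earlier and prevent the development of severe hypoxemia". Section 2 describes the device as one "which is expected to be able to detect respiratory abnormalities and their cause prior to the development of hypoxemia".
- **A response is possible without desaturation.** For apnea of 20 seconds or more with no fall in SpO2, section 5.7 says "the doctor in charge of sedation will consider response measures, including observation".
- **There is no common reference trace in Phase III.** Footnote a to the schedule in section 7.1 says "only one of capnography or nasal pressure will be recorded and displayed". In Phase II both signals are recorded in the same patient, but the sedation doctor does not watch capnography.

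**The concern.** An SpO2 drop is not a neutral sampling point here. It happens after randomisation, and the assigned monitor guides the care meant to avoid it. If a warning is seen and acted on in time, no drop follows and the episode leaves the comparison. If it is missed, a drop follows and the episode stays. Each monitor is then judged on a set from which some of its own successes have been removed, and the share removed can differ by arm.

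A second weakness is separate from this. If only windows before a drop are read, nothing shows how often the same waveform changes occur when no drop follows. Non-specific variation is then counted as warning.

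What is at stake is the supporting evidence for the device's central claim, that it shows trouble before hypoxemia. The non-inferiority conclusion is not at stake.

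**Working it through.** **The plan's own figures.** No figure in the Protocol bears directly on this comparison. The Phase III size does reproduce: (1.960 + 0.8416)² × 2 × 0.20 × 0.80 / 0.15² = 111.6, rounded up to 112 per arm and 224 in total. It does not depend on section 10.3.

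**Inputs.** Let d be the share of abnormal episodes in which the monitor shows a warning, and a the share of warned episodes that are averted. Neither is in the documents, so every value below is an assumption.

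**Selection effect.** Of all episodes, d(1−a) are warned but still end in a drop, and 1−d are unwarned and end in a drop. Hence:

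- share of episodes ending in a drop = 1 − d·a
- apparent detection among drops = d(1−a) / (1 − d·a)

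Equivalently, the odds of detection are multiplied by (1−a).

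| Better monitor (d, a) | Worse monitor (d, a) | Drops per 100 episodes | Apparent detection | Ranking |
|---|---|---|---|---|
| 0.80, 0 | 0.60, 0 | 100 v 100 | 80% v 60% | kept, undistorted |
| 0.80, 0.70 | 0.50, 0.70 | 44 v 65 | 0.24/0.44 = 55% v 0.15/0.65 = 23% | kept, both too low |
| 0.80, 0.75 | 0.50, 0.25 | 40 v 87.5 | 50% v 43% | kept, gap 7 points instead of 30 |
| 0.80, 0.90 | 0.50, 0.30 | 28 v 85 | 0.08/0.28 = 29% v 0.35/0.85 = 41% | reversed |

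**When the ranking reverses.** It reverses when (1−a_better)/(1−a_worse) is below odds(d_worse)/odds(d_better). For 80% v 50% detection the odds are 4 and 1, so the limit is 1/4: the better monitor's non-averted share must be under one quarter of the worse monitor's. In the last row it is 0.10/0.70 = 0.14, which is below the limit. In the third row it is 0.25/0.75 = 0.33, which is not.

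**Non-specific changes.** Let d′ be the true share of drops preceded by a real warning and f the share of windows with a spurious change. Windows before a drop then show d′ + (1−d′)f. A trace with no information (d′ = 0) scores 20% at f = 0.20 and 40% at f = 0.40. Control windows would show f, and the difference between the two kinds of window is d′(1−f), which is zero for that trace, as it should be.

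**The case against.** The strongest reply is that this is one explanatory sentence for an exploratory item. It sets no denominator, window or test, and sections 11.5.2.1 and 11.5.2.2 attach tests only to the primary and secondary endpoints. That stands, and it limits the weight of the point. The sentence nevertheless fixes which waveforms are compared between arms, and that choice is what distorts.

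A reader might infer several stronger things that the documents do not support:

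- **That averted episodes vanish from the trial.** They do not. Apnea of 20 seconds or more is a secondary endpoint counted from the monitor records, and section 10.3 also compares how often depression and obstruction patterns occur in both groups. These are counts rather than detection rates, but they can include averted episodes.
- **That what remains is mostly missed episodes.** This depends on the inputs. The missed share of drops is (1−d)/(1−d·a): 0.20/0.28 = 71% at d = 0.80, a = 0.90, but 0.20/0.44 = 45% at a = 0.70. Moreover, apart from apnea, the triggers in sections 5.6 and 5.7 already require SpO2 below 95% or below 90%. If a drop in section 10.3 includes values under 95%, many acted-on episodes stay in.
- **That the ranking will reverse.** It can, but only with a large difference in aversion. The reversed row implies 28 v 85 drops per 100 episodes. If drops meant values under 90%, such a gap should be visible in the primary endpoint.
- **That nothing without a drop is read.** The false-alarm item (section 7.1, footnote c) covers absence of waveform for more than three minutes without desaturation, and footnote d covers dislodged sensors. Both are too coarse for the small waveform changes that section 10.3 has in mind.
- **That redefining episodes by waveform repairs Phase III.** It does not. Each arm stores only its own signal, so an episode invisible on that signal would never enter its denominator, and detection would tend towards 100% in both arms. An SpO2 drop is at least recorded in the same way in both arms.

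**Conclusion.** The point holds in a limited form. The between-arm detection comparison in section 10.3 selects on a post-randomisation event that the assigned monitor is meant to prevent. Without drop-free windows it also cannot separate real warning from non-specific change. Distortion follows whenever some warned episodes are averted, and in the equal-aversion example it lowers 80% v 50% to 55% v 23%. Reversal is possible but needs the better monitor also to avert a much larger share of what it detects.

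All magnitudes rest on assumed detection and aversion rates, and the loss is smaller if the undefined drop includes values under 95%. The endpoint is exploratory; the primary analysis and the sample size are untouched. The change is worth making because it is cheap and because early detection is the stated reason for the device.

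**What to change.** Revise section 10.3, and carry the detail into the SAP:

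1. **Control windows.** For each SpO2 drop, also read matched windows of the same length without a drop, from the stored records, with the reader unaware of the SpO2 trace. Report the waveform-change rate in both kinds of window, by arm. This addresses non-specific change, not the selection.
2. **Head-to-head detection in Phase II.** Both signals are recorded there in the same patient. Compare them over all episodes visible on either trace or followed by a drop. State that care was guided by nasal pressure, so the two traces did not have equal influence on what happened next.
3. **Phase III drop-only comparison as descriptive.** State its SpO2 threshold. Show it beside the arm-specific frequency of drops, and of apnea or responses without a drop. Responses should be retrievable because, under section 5.6, "details regarding the respiratory abnormality that caused them are recorded in the check sheet". Draw no ranking of the monitors from it.
4. **No waveform-defined denominator in Phase III**, since each arm records only its own signal.

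The cost is a change of wording and extra reading of stored waveforms by the assistant investigators who already analyse them. No new data are collected.
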